## Abstract

**Introduction:**

Smoke-free public places legislation has been introduced in many countries to protect the public from the harmful effects of secondhand smoking. While evaluations of smoke-free policies have demonstrated major public health benefits, the impact on youth smoking and inequalities in smoking remains unclear. This project aims to evaluate how smoke-free public places legislation in the UK has impacted on inequalities in youth smoking uptake, and how much of any impact is via changes in parental smoking behaviour.

**Methods and analysis:**

The study will constitute secondary analyses of UK data (from the British Household Panel Survey and the Understanding Society study). Merging these datasets gives coverage of the period from 1994 to 2016. Missing data will be handled using multiple imputation. The primary outcomes are the rates and inequalities in initiation, experimentation, escalation to daily smoking and quitting among youths aged 11–15 years. Secondary outcomes include the prevalence of smoking among parents of these youths. Discrete-time event history analysis will be conducted to examine whether changes in the probability of youth smoking transitions are associated with the implementation of the smoke-free public places legislation; and whether any observed effects differ by socioeconomic position and parental smoking. A multilevel logistic regression model will be used to investigate whether there is a step change or change in trend for the prevalence of parental smoking after the policy was implemented. The models will be adjusted for relevant factors (including cigarette taxation, the change in the legal age for purchase of cigarettes and e-cigarette prevalence) that may be associated with the implementation of the legislation.

**Ethics and dissemination:**

This project will use anonymised survey data which have been collected following independent ethical review. The dissemination of the study findings will adopt multiple communication channels targeting both scientific and non-scientific audiences.

Strengths and limitations of this studyThe study will provide novel evidence on the impact of UK smoke-free public places legislation on inequalities in distinct stages of youth smoking uptake.We use household data to investigate changes in parental smoking as one potential mechanism by which the legislation may impact on youth smoking uptake (or inequalities therein).Causal attribution of observed changes to the smoke-free legislation rests on the assumption that this was the only relevant change occurring at this point in time.Nevertheless, we plan sensitivity analyses to adjust for other relevant policy changes and strengthen the case that any observed impacts are specifically associated with the smoke-free legislation.

## Introduction

Tobacco smoking remains a major cause of death and disability around the world, as well as a major contributor to health inequalities.^1 2^ Socioeconomic inequalities in youth smoking uptake are an important driver of adult inequalities in smoking,^3–5^ as the habit is difficult to quit once established. Tackling the uptake of smoking among adolescents is, therefore, a key aspect of achieving national goals for a smoke-free generation.^1 6 7^

Smoke-free public places legislation^8^ has been introduced in many countries to protect the public, especially non-smokers, from the harmful effects of secondhand smoking (SHS). Evaluations of smoke-free policy have demonstrated it has had major public health benefits, including reducing rates of heart attack and pregnancy-related complications.^8–13^ Positive impacts on child health have also been seen, with smoke-free public places policy linked to reductions in childhood asthma hospitalisations.^9^ However, a recent Cochrane systematic review found sparse and inconsistent evidence as to the impact of such policies on inequalities in smoking prevalence and even sparser evidence regarding the policies’ impacts on overall and inequalities in smoking uptake among young people.^8^ One study of smoking prevalence among adolescents aged 13 and 15years in the UK has suggested a drop in prevalence after legislation, particularly for females, but did not examine socioeconomic inequalities.^14^

Although its primary purpose was to prevent harm to the public, especially non-smokers, from SHS, the smoke-free public places legislation in the UK was also expected to improve air quality in public places and reduce health risks associated with smoking among smokers.^15^ Importantly, the legislation was also expected to contribute to changes in social attitudes and norms towards smoking by reducing the acceptability of smoking, especially in social places like pubs and restaurants and other public spaces shared with non-smokers.^16 17^ For example, research on implementation of smoke-free legislation in Massachusetts, USA, showed that smoking became less socially acceptable, and social norms shifted to favour smoke-free environments.^18^ Impacts on adult behaviour and societal norms are critical to understanding how and why a ban might impact on youth smoking, as youths are unlikely to smoke in the public places affected by the legislation. Any effect on youth smoking could be through changes in adult smoking behaviour, and the implications this has for social norms and the availability of cigarettes to young people given that adults are a major source of cigarettes for youth smokers.^19 20^ Thus, effects of legislation may not be immediate but may grow over the years following the implementation of the legislation as these effects accumulate.

Parental smoking is a key influence on children’s smoking uptake,^5 21^ and thus may be a major mechanism by which smoke-free legislation impacts on youth smoking. There are at least two potential mechanisms: impacts on the prevalence of parental smoking and displacement of smoking behaviour (see figure 1). First, regarding the prevalence of parental smoking, while studies tend not to show long-term effects of legislation on overall smoking prevalence, heterogeneity of impact among subgroups of smokers is still largely unexplored.^8 22^ Smokers who live with their children are one subgroup among whom smoking legislation and its associated social changes might be expected to have a stronger impact. Social denormalisation of smoking via smoke-free legislation may raise adults’ consciousness and awareness of potential harms, especially around children and non-smokers.^23^ Concerns about the health of children may then provoke cessation attempts. If parental smoking reduces after a ban, then decreases in youth uptake might be expected to follow.

**Figure 1 F1:**
[figure not shown]
Conceptual framework for the impact of smoke-free public places legislation on youth smoking transition.

Another potential, and not mutually exclusive, impact of smoke-free legislation is displacement of parental smoking behaviour (ie, not whether but where parents smoke). The displacement could be into or out of less regulated environments such as the home,^24 25^ which could influence children’s exposure to smoking behaviour. Indeed, biomarker data from one US study have indicated increased exposure to cigarette smoke among children living with smokers after public smoking bans.^26^ Nevertheless, evidence for displacement into the home is inconsistent: several studies have shown reductions rather than increases in the prevalence of smoking at home after smoke-free legislation^27 28^ and more voluntary smoke-free homes,^23 29–36^ especially homes with youths aged 15 years or less.^37^ If smoking is displaced out of the home, this may both reduce youths’ exposure to SHS and potentially reduce the uptake of smoking in children^38^ by weakening the influence of parental smoking on youth uptake. Alternatively, if parental smoking was displaced into homes, then the reverse could be true: an increase in uptake due to a strengthening of the influence of parental smoking.

Inconsistencies in existing evidence suggest heterogeneity in effects of the smoke-free public places legislation, so it is vital to explore the effects on inequalities. Considering the likely importance of parental smoking in any impact of legislation on youth uptake and that young people from disadvantaged backgrounds are more likely to have parents who smoke, it is likely that inequalities in youth uptake will be affected. Particularly, if more advantaged smoking parents are more likely to quit or stop smoking at home after a ban, or if disadvantaged smoking parents are more likely to displace their smoking behaviour into the home, then inequalities in youth uptake might be expected to widen. Indeed, initial data using salivary cotinine samples from school children before and after implementation of UK bans do suggest a widening of inequalities in children’s exposure to smoking, with greater decreases in exposure among the more affluent.^39 40^

Randomised controlled trials, often seen as the gold standard for establishing causality, are ethically and practically problematic in the context of studying population-level policies such as the smoke-free legislation. However, implementation of smoke-free public places legislation in the UK, which occurred in 2006 in Scotland and 2007 in the rest of the UK, provides the opportunity for a natural experimental approach^41^ to studying the impact of this policy on youth uptake, and the mechanisms by which these impacts occur. A natural experimental approach requires weaker assumptions for observed effects to be interpreted as causal than in most observational epidemiological studies. Specifically, if we were to observe that both parental smoking and the implementation of smoke-free legislation were associated with youth smoking uptake (thinking of parental smoking generally rather than in the context of this policy change), then causal interpretations of these associations both require an assumption of no (unmeasured) confounding. However, this assumption is considerably stronger for parental smoking (ie, that no other factor is causing both parental smoking and youth smoking) than for the timing of the legislation (ie, that no other factor causing/coinciding with the implementation of the legislation implementation also causes changes in youth smoking uptake).

Nevertheless, even for the implementation of smoke-free legislation, the assumption of no confounding may be problematic as the policy has not been the only important change happening in the UK that might impact on youth smoking uptake. Though acknowledged as one of the most significant changes in policy, smoke-free legislation was implemented in the UK within a period of incrementally increasing tobacco control.^42^ For example, sales taxes applied to cigarettes are subject to ongoing change, and the implementation of smoke-free legislation also coincided closely with a 2007 change in the legal age for purchase of cigarettes from 16 to 18 years. Another factor is the availability and use of e-cigarettes which has been growing in the UK since 2011.^43^ To attribute changes in youth smoking to the smoke-free policies, we will need to differentiate the impacts of the policy from these other contextual changes.

### Aims/objectives/research questions

This project aims to evaluate how the implementation of the smoke-free public places legislation in the UK has impacted on inequalities in youth smoking uptake. Further, we will investigate how much (if any) of the impact is due to impacts of the ban on the smoking behaviour of youths’ parents. We will seek to differentiate the effects of the smoke-free public places legislation from other changes happening in the UK such as increases in the legal age for purchasing cigarettes, the rising prevalence of e-cigarettes and the changes in tobacco taxation in the UK.

To ensure this study covers appropriate ages with regards to smoking uptake, we will focus on youths aged 11–15 years. We focus on smoking uptake within this age group because young people who establish a daily smoking habit by age 15 are less likely to quit or reduce their smoking as they move into adulthood.^21 44–46^ Smoking uptake in this study is defined as a series of transitions: initiation, representing initial trying; experimentation or progression from initial trying to occasional use; escalation from occasional to daily use and quitting (see figure 2).^47^

**Figure 2 F2:**
[figure not shown]
Smoking stages for early adolescents. Adapted from ‘Socioeconomic position and early adolescent smoking development: evidence from the British Youth Panel Survey (1994–2008)’ by Green *et al*.^47^

Using population representative longitudinal survey data, we will address the following research questions:Q1. Has the implementation of the smoke-free public places legislation in the UK been associated with a step change or change in the trend in the probability of youth smoking transitions?Q2. Has the implementation of the smoke-free public places legislation in the UK been associated with a step change or change in the trend in the inequalities in the probability of youth smoking transitions?Q3. (A) Has the implementation of the smoke-free public places legislation in the UK been associated with a step change or change in the trend in the prevalence of smoking among parents of UK youths? (B) Does the observed change (if any) differ by socioeconomic position?Q4. (A) Do changes in parental smoking explain any impact of the smoke-free public places legislation on the probability of youth smoking transitions? (B) Has the implementation of the smoke-free public places legislation in the UK been associated with any change in the strength of the association between parental smoking and the probability of youth transitions? (C) Does the observed change (if any) differ by socioeconomic position?Q5. How distinct are the impacts of the smoke-free public places legislation from the impacts of the change in the legal age for purchasing tobacco, the increasing prevalence of e-cigarettes and the changes in tobacco taxation on youth smoking transition?

## Methods and analysis

### Study design

The study will constitute secondary analyses of UK survey data (see section on Data). The control group will be all UK youths aged 11–15 years prior to the implementation of the smoking ban (in 2006 for youths living in Scotland and 2007 for those living elsewhere in the UK). The intervention group is all UK youths aged 11–15 years after the implementation of the ban. The primary outcomes of interest are the rates of initiation, experimentation, escalation to daily smoking and quitting within this age group. A secondary outcome of interest is the prevalence of smoking among parents of these youths. The causal interpretation of the differences between these groups rests on the assumption that the implementation of the smoke-free public places legislation is the only relevant difference between these groups and that there are no other systematic differences between these groups that would account for their differences in outcomes.

### Data

Data from the British Household Panel Survey (BHPS) Youth Sub-Sample and Understanding Society, both of which are freely available to bona fide researchers from the UK Data Archive under their normal terms and conditions,^48 49^ will be used in this study. Both Understanding Society and BHPS studies obtained consent for data sharing from their participants. More information on the data sources, consent and sampling can be found on BHPS and Understanding Society websites https://www.iser.essex.ac.uk/bhps and https://www.understandingsociety.ac.uk/, respectively. Data on youths’ (11–15 year olds) and parents’ smoking history, and parents’ socioeconomic position from the BHPS (covering the period 1994–2009) will be merged with those of the recent Understanding Society Survey (from 2009 to 2016). The merger of these datasets gives coverage of the period from 1994 to 2016, with data from 2016 newly released in November 2017. As such, 9–10 years of postlegislation data will be available in the dataset. This amount of postlegislation data will be important in investigating the immediate as well as the long-term impact of the smoke-free public places legislation on youths smoking transition. Respondents will be included for each year they were aged 11–15 within this period (ie, a maximum of 5 years of data per respondent).

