### Statistical analysis

Discrete-time event history analysis^53^ will be conducted to examine whether changes in the probability of youth smoking transitions are associated with the implementation of the smoke-free public places legislation (Q1). The implementation of smoke-free legislation is viewed as a natural experiment,^41 54^ and analyses will examine if there is a step change or change in trend in the probability of smoking transitions after the country-specific implementation dates for the smoke-free legislation (ie, 2006 for Scotland, 2007 for the rest of the UK). Youth will only be considered at risk for a transition once they have made the previous transition (ie, they are only at risk for experimentation once they have tried smoking). Thus, data for each analysis will be right censored at the year of the smoking transition (or age 15 years) and left censored prior to the previous transition (or age 11 years). Escalation to daily smoking and quitting will be treated as two alternative outcomes, which young people will be at risk of once they commence occasional smoking. In line with previous work,^47^ youths who skipped smoking transition stages will be treated as making the intervening transitions in the same year. For instance, youths who transited from never having tried smoking to ex-smoker in the same year will be treated as having progressed to occasional smoker and having quit within the same year (but not as having escalated to daily smoking). Analyses will be adjusted for age, gender, the overall temporal trend in rates (which may encompass effects of other temporal increases in tobacco control) and overall differences in rates between UK countries.

We will then examine whether any effects observed on youth smoking transition differ by socioeconomic position (Q2). Parental education level will be used as an indicator of socioeconomic position. In cases where parental educational qualification for both parents differs, the higher qualification will be used. This will be added to the predictive models, alongside interactions with the variables representing the implementation of the legislation.

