A multilevel logistic regression model (with person-years nested within persons) will be used to investigate whether there is a step change or change in trend for the prevalence of parental smoking (any current smoking by either parent) after smoke-free public places legislations were implemented in the UK (Q3A) and whether observed changes (if any) differ by socioeconomic position (Q3B). This model will include all years of data for all respondents without any right or left censoring and will be adjusted for the young person’s age, gender, the overall temporal trend in parental smoking and overall differences between UK countries. The second stage of the modelling will additionally include parental education and interactions between parental education and the variables representing the implementation of the legislation.

Next, building on the models developed to assess whether the impact of the legislation on youth smoking transitions varied by socioeconomic position (Q2), parental smoking will also be included and we will assess whether this explains any observed differences associated with the implementation of the legislation (Q4A). We will test for interactions between parental smoking and the variables representing the implementation of the legislation to see if the influence of parental smoking changes after the legislation (Q4B) and then for a three-way interaction between parental smoking, legislation implementation and socioeconomic position to see if this varies by socioeconomic position (Q4C).

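### The data source changes from BHPS to Understanding Society in 2009, inside the post-ban period, and no listed model or sensitivity analysis accounts for it

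*Protocol article*

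**What the plan says.** The Data section states that youth and parent data "from the BHPS (covering the period 1994–2009) will be merged with those of the recent Understanding Society Survey (from 2009 to 2016"). It draws the consequence "As such, 9–10 years of postlegislation data will be available in the dataset" and presents that span as what allows long-term as well as immediate impact to be studied.

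Under Statistical analysis the ban dates are given as "ie, 2006 for Scotland, 2007 for the rest of the UK", and "analyses will examine if there is a step change or change in trend in the probability of smoking transitions". For the youth models, "Analyses will be adjusted for age, gender, the overall temporal trend in rates", and also for UK country. The parental smoking model is "adjusted for the young person’s age, gender, the overall temporal trend in parental smoking and overall differences between UK countries". Later stages add parental education, parental smoking and their interactions with the legislation variables. The last stage adds cigarette tax, legal purchase age and e-cigarette prevalence. The only further check moves the ban date 5 years either way.

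Source survey appears in none of these lists and is not mentioned under Handling missing data. The Limitations section discusses competing policies but not the change of survey.

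**The concern.** The Study design section rests causal interpretation on there being no other systematic difference between the pre-ban and post-ban groups. Source survey is such a difference, and it is built in: before the ban it is always BHPS; after it, mostly Understanding Society. If the two surveys differ in who is sampled, who responds or how smoking is asked, the outcome level shifts two to three years after the ban for reasons unrelated to it.

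The estimates most exposed are the change in trend and the long-term impact, because they depend mainly on Understanding Society years. The same holds for parental smoking (Q3). It also holds for the inequality and parental-smoking interactions (Q2–Q4) if the surveys differ in those gradients.

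**Working it through.** **Dates.** The stated post-ban span reproduces: 2016 − 2007 = 9 years and 2016 − 2006 = 10 years. Outside Scotland the post-ban calendar years are 2007–2016, ten in all. Understanding Society supplies 8 of them if it takes over in 2009 and 7 if in 2010; the document gives 2009 for both surveys.

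**Method.** Let s = 1 for Understanding Society and 0 for BHPS, and let D be an assumed level difference in log-odds. Project s on the planned terms (constant, time, step, post-ban slope change), a linear approximation to the logistic model. The coefficients are the shares of D that each term absorbs when the ban has no effect.

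**By hand, switch in 2009, equal weight per year, ban in 2007.** A step and a slope change together fit a separate line to each period. Before the ban s = 0 throughout, so the pre-ban trend takes nothing. After the ban, with t = 0,…,9:

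- mean t = 4.5; sum of (t − 4.5)² = 82.5; mean s = 8/10 = 0.8
- sum of (t − 4.5)s over t = 2,…,9: 44 − 8 × 4.5 = 8
- slope change = 8/82.5 = 0.097 D per year
- step = 0.8 − 4.5 × 0.097 = 0.364 D
- total by 2016 = 0.364 + 9 × 0.097 = 1.24 D

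**Range.** Assumptions not in the document: switch year 2009 or 2010; Understanding Society person-years per year 1 or 3 times those of BHPS.

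| Switch | Weight | Step | Slope change per year | Total by 2016 | SE ratio with survey term: step / slope |
|---|---|---|---|---|---|
| 2009 | 1× | 0.36 D | 0.097 D | 1.24 D | 1.11 / 1.28 |
| 2009 | 3× | 0.65 D | 0.054 D | 1.13 D | 1.26 / 1.09 |
| 2010 | 1× | 0.13 D | 0.127 D | 1.27 D | 1.02 / 1.48 |
| 2010 | 3× | 0.41 D | 0.087 D | 1.19 D | 1.09 / 1.19 |

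With country-specific ban dates and assumed country weights (England 0.83, Scotland 0.09, Wales 0.05, Northern Ireland 0.03) the picture is the same: step 0.12–0.63 D and slope change 0.055–0.127 D per year. The planned terms explain 83–85% of the variation in s; the rest is residual.

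**Illustration.** D is unknown. If D were 0.05, 0.10 or 0.20, the spurious ban effect by 2016 would be 0.06, 0.11–0.13 or 0.23–0.25. A negative D reverses the sign.

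**Other planned models.**

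- Step only: with country-specific dates, the step takes 0.22–0.59 D and the overall trend 0.03–0.04 D per year.
- Step and slope plus an e-cigarette term, assumed to rise linearly from 2012, with tax not modelled: step −0.20 to +0.23 D, slope change 0.22–0.30 D per year, e-cigarette coefficient −0.25 to −0.32 D per unit. The survey difference is then split between ban and e-cigarette effects, and both are distorted.

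**Placebo test.** Under a pure survey shift, the slope change at the date 5 years earlier is 0.09–0.10 D per year. That equals or exceeds the true-date value in 3 of the 4 scenarios. The step at the date 5 years later exceeds the true-date step in 2 of 4.

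**The case against.** The best case against is that no survey difference is documented, so the bias may be nil. That is correct: size and direction are unknown, and it would be wrong to infer that the surveys are known to differ. What stands is that the listed models could not reveal a difference if there were one.

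Second, the placebo test offers some protection, because a survey artefact would often give placebo slopes as large as the real one. This stands as a warning only. A genuine effect growing from 2007 would also leave a slope change at an earlier placebo date, so the test neither names the survey as the cause nor removes its effect.

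Third, a reader might infer that every survey difference is always reported as a ban effect. That holds closely only for the step-plus-slope models. In a step-only model the overall trend takes part, and in the final models the e-cigarette term does.

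Fourth, a reader might infer that the switch also creates a burst of false events, from youths already smoking at their first Understanding Society interview. The text does not support this. The rule that "youths who skipped smoking transition stages will be treated as making the intervening transitions in the same year" is illustrated by an observed jump between stages. The article does not say that youths first seen as smokers are given an event in their entry year.

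Last, brevity is no defence here, because the article spells out the adjustment set model by model.

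**Conclusion.** The point holds. All pre-ban data are BHPS, most post-ban data are Understanding Society, and neither the listed models nor the sensitivity analyses account for it. In the step-plus-slope models a survey level difference D falls almost wholly on the ban terms and reaches about 1.1–1.3 D by 2016. This rests on a linear approximation, a switch in 2009 or 2010, and the assumed relative survey sizes. The conclusion is that the plan cannot tell a survey difference from a ban effect, not that the results will be biased by any particular amount.

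**What to change.** 1. Rerun every youth and parent model with a survey indicator. For the Q2–Q4 interactions add survey-by-education and survey-by-parental-smoking terms, since a main effect alone does not protect them. Include survey in the imputation model. The indicator is estimable because BHPS itself covers about 2–4 post-ban calendar years.
2. Repeat the step-change analysis in BHPS alone (1994–2009).
3. Name the change of survey under Limitations, and do not attribute a long-term trend change to the ban if it disappears in item 1.

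No new data are needed. The cost is extra analysis and lower precision: the step SE rises about 2–26% and the slope-change SE about 9–48%, or to about 1.5–2.2 times its size once an e-cigarette term is in the model. The Introduction expects effects that build up over years, and a survey term may absorb part of a genuine delayed effect. Results should therefore be shown with and without it.
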